#### 3.1.3. Stage Three

If the efficacy of CHM on CHF is better than placebo in Stage Two, we will conduct Stage Three to evaluate the feasibility, compliance, and universality and make cost-effectiveness analysis of CHM on CHF based on syndrome differentiation. A flowchart of the third stage is shown in Figure 3.

*Diagnostic Criteria*

*Diagnostic Criteria for CHF*. Diagnostic criteria are the same as those of Stage Two.

*Diagnostic Criteria for TCM Syndrome Differentiation*. Diagnostic criteria were the same as those of Stage Two.

*Inclusion Criteria for Participants*. Patients who accorded with diagnostic criteria were potentially eligible for the study if they met the following criteria.The primary heart disease is CHD (with diagnosis for CHD confirmed by coronary angiography, coronary computed tomography, history of acute myocardial infarction, limb-salvage Q wave for electrocardiogram (ECG), ECG test, radionuclide examination support, etc.). The included patients also had no history of hypertension or taking antihypertensive drugs, with a blood pressure under 160/100 mmHg.With a history of CHD, the following symptoms and signs were observed: difficult breathing, fatigue, and fluid retention (edema), with left ventricular enlargement, along with increasing of left ventricular end systolic volume and LVEF ≤ 50%, with NYHA cardiac function II or III.Male or female patients should be between 40 and 75 years old.

If there is any violation of those criteria, the subject could not participate into this research.

*Exclusion Criteria for Participants*. Exclusion criteria were the same as those in Stage Two.

*Sample Size*. This design in this stage is to show the superiority of TCM based on syndrome differentiation. The ratio in this stage is 1 : 1. The sample size calculation is based on LVEF of Stage Two. To calculate the sample size, we will use the following formula (*δ* = 2):(2)$$\begin{array}{c} n=\frac{\left({\left(Z_{1-a/2}+Z_{1-\beta }\right)}^{2}*\left(\sigma_{1}^{2}+\sigma_{2}^{2}\right)\right)}{{\left(\varepsilon -\delta \right)}^{2}}. \end{array}$$

And the maximum dropout is 10%.

*Randomization*. All participants in this stage will be randomly distributed to CHM or placebo group according to random number sequence.

*Setting*. In this stage, five or more centers will take part in the trial.

*Interventions*. Besides standardized western medicine treatment, participants in CHM group will receive CHM based on syndrome differentiation. Control Group will receive standardized western medicine only.

CHM granules will be prepared as in Stage Two.

*Outcome Measurements*. In this stage, the primary outcome measurement is LVEF. Secondary outcome measurements are 6MWT, TCM syndrome scores, and NYHA functional classification. Meanwhile, the feasibility, cost-effectiveness analysis, compliance, and universality will be evaluated or performed. Feasibility and universality investigation of this research will be executed by the questionnaire of doctors and patients; compliance evaluation will be executed by the ratio between the actual amount of medication and the supposed amount in CHM group; cost effectiveness will be conducted by the ratio between the different improved condition of LVEF and treatment costs. Side effects will be monitored during the trial period. Biological indicators (blood routine examination, liver function, kidney function, and ECG) will be tested before and after the treatment. The timeline of participants through Stage Three is shown in Table 5.

*Statistical Analysis*. Data will be analyzed on the Intention-to-Treat (ITT) analysis and the per-protocol set (PPS) for coherence. The basic characteristics will be compared with independent samples *t*-test for continuous variables and chi-square analyses for categorical variables. The measurement data will be expressed as mean ± standard deviation for us to check the data of all groups with normal test and variance homogeneity test. The changes in measurement data between baseline and the assessment for four weeks will be performed with independent samples *t*-test. The categorical variables will be compared with chi-square analyses. Safety analysis will be conducted. Results will be shown with 95% confidence intervals (CIs). The level of significance will be set at 0.05. If *P* < 0.05, there will be statistical differences. All tests will be 2-tailed.

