#### 3.1.2. Stage Two

The second stage of this trial was a multicentral, randomized clinical trial with placebo-controlled and double-blind methods.  Figure 2 shows the trial flowchart. 

*Diagnostic Criteria*

*Diagnostic Criteria for CHF*. Diagnostic criteria were as follows: (1) diagnostic criteria of CHF:* 2007 China Guideline for the Diagnosis and Treatment of CHF* [5]; (2) heart function standard:* The Criteria for Diagnosis and Treatment of Heart Disease *first published by the New York Heart Association (NYHA) [11]. 

*Diagnostic Criteria for TCM Syndrome Differentiation*. Diagnostic criteria were as follows: TCM differentiation standard: according to the* Guiding Principles for the Clinical Study of New Drugs in Traditional Chinese Medicine* released in 2002 [12]. 

*Inclusion Criteria for Participants*. Patients who accorded with diagnostic criteria were potentially eligible for the study if they met the following criteria.The primary heart disease is CHD (with diagnosis for CHD confirmed by coronary angiography, coronary computed tomography, history of acute myocardial infarction, limb-salvage Q wave for electrocardiogram (ECG), ECG test, radionuclide examination support, etc.). The included patients should have no history of hypertension or taking antihypertensive drugs, with a blood pressure under 160/100 mmHg.With a history of CHD, the following symptoms and signs were observed: difficult breathing, fatigue, fluid retention (edema), left ventricular enlargement, systolic volume of left ventricular increase with LVEF ≤ 40%, and NYHA functional classification II or III.Male or female patients should be between 40 and 75 years old.If there was any violation of those criteria, the subject could not participate in this research.

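### Stage Three admits LVEF up to 50%, but its trigger and sample-size inputs come from Stage Two patients with LVEF up to 40%, so they are unsupported for the added stratum

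*Protocol article*

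**What the plan says.** The Stage Two inclusion criteria (section 3.1.2) require "systolic volume of left ventricular increase with LVEF ≤ 40%, and NYHA functional classification II or III". The Stage Three inclusion criteria (section 3.1.3) are otherwise nearly the same list but read "left ventricular end systolic volume and LVEF ≤ 50%, with NYHA cardiac function II or III". Section 3.1.3 declares the diagnostic and exclusion criteria unchanged from Stage Two. It does not mention that the LVEF ceiling has moved.

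Two links tie Stage Three to Stage Two. The first is the trigger: "If the efficacy of CHM on CHF is better than placebo in Stage Two, we will conduct Stage Three". The second is the sizing rule: "The sample size calculation is based on LVEF of Stage Two". Formula (2) takes an effect ε and variances σ₁² and σ₂² and subtracts δ = 2 from the effect. Allocation is 1:1 and the dropout allowance is 10%. No ε, σ, power or total is given.

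LVEF is the primary outcome in both stages. Stage Two used stratified blocked randomisation; for Stage Three only a random number sequence is named. The Stage Three analysis is an independent-samples t-test on the change from baseline to four weeks, two-tailed at 0.05, with no LVEF stratum or baseline covariate.

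**The concern.** A sample-size input carries over from one trial to the next only as far as the populations match. Here the mismatch lies in the baseline value of the primary endpoint. No patient was eligible for Stage Two with an LVEF above 40%, so Stage Two cannot supply an effect or a standard deviation for that range, nor show that the treatment works there.

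Nothing in the Stage Three plan absorbs this. Randomisation is not described as stratified by LVEF, the test is unadjusted, and no result by LVEF range is planned. The cost-effectiveness ratio also uses LVEF improvement, so it mixes the two ranges as well. If Stage Three is negative, a reader cannot tell whether the Stage Two effect failed to replicate or was diluted by the added patients. If it is positive, the extent to which it confirms Stage Two is unclear.

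**Working it through.** There is no stated Stage Three sample size to reproduce. What can be checked is how strongly formula (2) reacts when its inputs move.

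**Inputs from the article (section 3.1.3):** ceilings of 40% and 50%; δ = 2 (unit not stated, taken as LVEF percentage points); two-sided α = 0.05; 1:1 allocation; 10% dropout.

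**Assumptions, not in the article:** 80% power; Stage Two ε of 4 or 5 points; SD of 8; and, for the dilution example, 40% of patients above LVEF 40% with half the effect.

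**Formula (2):** n per arm = (z₀.₉₇₅ + z₀.₈₀)² (σ₁² + σ₂²) / (ε − δ)², where z₀.₉₇₅ + z₀.₈₀ = 1.9600 + 0.8416 = 2.8016. With SD 8:

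| ε | n per arm | total after 10% dropout |
|---|---|---|
| 4 | 252 | 560 |
| 5 | 112 | 249 |
| 6 | 63 | 140 |

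**Dilution example.**
1. Overall effect: 4 × (0.6 + 0.4 × 0.5) = 3.2.
2. Sizing on ε − δ = 2 at 80% power fixes the standard error at 2 / 2.8016 = 0.714.
3. Power against the margin: the distance is 3.2 − 2 = 1.2, which is 0.6 of the planned 2. Φ(2.8016 × 0.6 − 1.96) = Φ(−0.279) ≈ 39%.
4. Power against zero: 3.2 / 2 = 1.6. Φ(2.8016 × 1.6 − 1.96) = Φ(2.523) ≈ 99%.

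A 20% loss of effect removes 40% of the distance that formula (2) relies on, because the margin is subtracted first. The n needed to restore power against the margin rises by (2 / 1.2)² = 2.78.

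**Other shifts, power against the margin:**

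| Change from planning value | Factor on n | Power |
|---|---|---|
| SD × 0.9 | 0.81 | 88% |
| SD × 1.10 | 1.21 | 72% |
| SD × 1.25 | 1.56 | 61% |
| SD × 1.50 | 2.25 | 46% |
| ε 5 → 4.5 | 1.44 | 65% |
| ε 5 → 4 | 2.25 | 46% |

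The first row shows that the error need not be harmful.

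**The case against.** Several points on the other side stand.

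- **Nested populations.** LVEF ≤ 40% lies inside LVEF ≤ 50%. Stage Two lacks data on one added stratum; it does not describe a different population.
- **No formal contradiction.** Only the diagnostic and exclusion criteria are declared the same. Stage Three aims at feasibility, universality and use in community health service centres, and wider entry fits that aim. The article does not give this as the reason, however, and the stage is still sized to show superiority on LVEF from Stage Two inputs.
- **No n exists yet.** Sizing from Stage Two data does not rule out an adjustment for the wider range, and a full protocol could hold one.

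A reader might go further and infer that both inputs are wrong and that Stage Three will be underpowered. The documents do not support that.

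- The test actually described is an ordinary t-test with no margin. In the dilution example it keeps about 99% power against zero. Even with an SD 1.5 times larger as well, it keeps Φ(4.483 / 1.5 − 1.96) ≈ 85%.
- A figure of Φ(2.8016 × 0.8 − 1.96) ≈ 61% against zero follows only if n was computed without a margin, and formula (2) has one.
- If LVEF were uniform from 20% upward, the wider range would raise the baseline variance by (30 / 20)² = 2.25. The planned analysis uses four-week change, and the variance of change could move either way.
- A smaller response above 40%, for lack of room to improve, is plausible, but nothing in the article shows it.

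**Conclusion.** The point holds as a gap in support. Stage Three carries over a trigger, an effect and a variance from LVEF ≤ 40% to LVEF ≤ 50%, gives no reason for the new ceiling, and plans nothing that would separate or adjust for the patients Stage Two did not study. This rests on the text alone.

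The size cannot be settled from the documents. The 39% against the margin of 2 and the 99% against zero both depend on assumed values: ε = 4, a 40% share above the old ceiling, half the effect there, and 80% power. They show how steeply formula (2) responds to a smaller effect and that the consequence depends on which hypothesis is tested. They do not show that Stage Three is underpowered, and the article gives no basis for saying which ceiling is right.

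**What to change.** Reconcile the two ceilings, or state why they differ. The trial status section says Stage Two was complete and Stage Three not yet begun, so this could be settled before enrolment. If LVEF ≤ 50% is kept:

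1. Stratify Stage Three randomisation at LVEF 40%. Baseline LVEF is already collected.
2. Replace the unadjusted t-test on change with an analysis adjusted for that stratum or for baseline LVEF.
3. Report the treatment effect in patients at or below 40% and in those above 40% up to 50%, with the treatment-by-stratum interaction.
4. State that the Stage Two ε and σ apply only to the lower stratum, and show n over a range of ε and σ for the wider population.

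The cost is one stratification factor, a little more analysis, and stratum estimates that will be imprecise. Restricting the confirmatory comparison to LVEF ≤ 40% is also possible but dearer: with an assumed 40% of patients above that level, filling the lower stratum to full n takes 1 / 0.6 ≈ 1.67 times the enrolment, and it works against the stage's universality aim.

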**Figure 3 fig3:**
[figure not shown]
The flowchart of Stage Three trial design.

**Table 1 tab1:** Databases search strategies.

Databases	Search terms
CNKI	[(Mesh terms = heart failure) OR (Title = chronic heart failure) OR (Keywords = chronic heart failure)] AND [(Mesh terms = syndrome) OR (Keywords = syndrome)]

CBM	(Mesh terms = chronic heart failure OR Mesh terms = CHF OR Mesh terms = chronic congestive heart failure OR Mesh terms = chronic cardiac insufficiency) and ((Mesh terms = syndrome) or (Mesh terms = traditional Chinese medicine))

VIP	((Title or keywords: chronic cardiac insufficiency) OR (Title or keywords: CHF) OR (Title or keywords: chronic heart failure) OR (Title or keywords: chronic congestive heart failure)) AND (Title or keywords: syndrome) AND (Title or keywords: symptom) AND (Medicine and health) AND (All Periodicals) AND (Year: 1994–2008)

**Table 2 tab2:** The distribution of symptoms in 176 literatures.

Symptom	Frequency	Rate (%)
Palpitation	233	5.6
Shortness of breath	160	3.9
Edema	159	3.8
Lassitude	153	3.7
Thread pulse	146	3.5
Dyspnea	126	3.0
Wheeze	117	2.8
Pale tongue	111	2.7
Intermittent pulse	110	2.7
Knotted pulse	110	2.7
Oliguria	101	2.4
Sweating	100	2.4

**Table 3 tab3:** The distribution of syndromes in 176 literatures.

Syndrome	Frequency	Rate (%)
Yang deficiency	6489	18.57
Qi deficiency	6377	18.25
Blood stasis	5731	16.40
Water retention	3445	9.86
Phlegm syndrome	973	2.78

**Table 4 tab4:** The timeline of participants' course through Stage Two.

Items	Baseline	Treatment	
	Visit 1	Visit 2	Visit 3
	0 weeks	2 weeks	4 weeks
Inclusion/exclusion	•		
Informed consent	•		
Grouping	•		
Medical history collection	•		
General information	•		
Medication history	•		
Physical examination	•		
Complicating diseases	•		
Drug release	•	•	
TCM syndrome scores	•	•	•
NYHA functional classification	•	•	•
6-minute walk test	•	•	•
LVEF	•	•	•
X-ray	•		
Routine urine test	•		•
Liver function test	•		•
Renal function test	•		•
Electrolytes	•		•
Electrocardiogram	•	•	•
Side effect		•	•

**Table 5 tab5:** The timeline of participants' course through Stage Three.

Items	Baseline	Treatment	
	Visit 1	Visit 2	Visit 3
	0 weeks	2 weeks	4 weeks
Inclusion/exclusion	•		
Informed consent	•		
Grouping	•		
Medical history collection	•		
General information	•		
Medication history	•		
Physical examination	•		
Complicating diseases	•		
Drug release	•	•	
TCM syndrome scores	•		•
NYHA functional classification	•		•
6-minute walk test	•		•
LVEF	•		•
X-ray	•		

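### Stage Three tests LVEF with an unadjusted t-test on change; the test is valid, but baseline-adjusted ANCOVA would be more precise at almost no cost

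*Protocol article*

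**What the plan says.** Section 3.1.3 (Stage Three) of the protocol article names the primary outcome: "In this stage, the primary outcome measurement is LVEF". It continues: "Secondary outcome measurements are 6MWT, TCM syndrome scores, and NYHA functional classification".

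The Statistical Analysis paragraph fixes the method for continuous outcomes: "The changes in measurement data between baseline and the assessment for four weeks will be performed with independent samples" *t*-test. For the rest it says: "The categorical variables will be compared with chi-square analyses". The test level and sidedness are also set: "The level of significance will be set at 0.05", and "All tests will be 2-tailed". No baseline covariate or ordinal method is named.

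Table 5 schedules LVEF, 6MWT, TCM syndrome scores and NYHA class at weeks 0 and 4. Patients enter "with NYHA cardiac function II or III" and with LVEF at or below 50%. The sample size paragraph gives a two-means formula with δ = 2, to be filled from the Stage Two LVEF results. It states no number of patients, SD, power or correlation for Stage Three.

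**The concern.** The article has chosen the primary analysis and has not left it open, and the choice is a weak one. A change score assumes that each unit of baseline LVEF carries over fully to week 4. Where the true slope is below 1, as regression to the mean would suggest in patients selected by an LVEF ceiling, subtracting the whole baseline value over-corrects and adds noise.

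Two things follow. The standard error of the LVEF difference is larger than it need be. And if the arms happen to differ at baseline, part of that difference stays in the estimate for that trial.

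The LVEF difference carries more than the superiority test, because the cost-effectiveness ratio in Stage Three is also built on LVEF improvement.

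**Working it through.** **Inputs from the article.** Continuous primary outcome; two-sided 0.05; 1:1 allocation; LVEF at weeks 0 and 4. There is no Stage Three sample size or power figure to reproduce.

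**Assumptions.** rho from 0.5 to 0.9; power of 80% for the planned test, as a reference point; equal baseline and week-4 SDs at first, then relaxed.

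**Variances (large sample).** Let the baseline SD be s and the week-4 SD be k·s. Per patient, in units of s²:
- change score: 1 + k² − 2·rho·k
- ANCOVA: k²(1 − rho²)
- difference: (1 − rho·k)², where rho·k is the slope of week-4 on baseline LVEF

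The difference cannot be negative, so ANCOVA is never less precise in large samples. The two agree only when the slope is exactly 1.

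**Equal SDs (k = 1).** The ratio ANCOVA/change is (1 − rho²)/[2(1 − rho)] = (1 + rho)/2. The standard error of the change score is larger by √[2/(1 + rho)]. Power with ANCOVA, when the change score has 80%, is Φ[(1.960 + 0.842)·√(2/(1 + rho)) − 1.960].

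| rho | Variance ratio | Patients saved | SE of change score vs ANCOVA | Power with ANCOVA |
|---|---|---|---|---|
| 0.5 | 0.75 | 25% | 1.15 | 90% |
| 0.7 | 0.85 | 15% | 1.08 | 86% |
| 0.8 | 0.90 | 10% | 1.05 | 84% |
| 0.9 | 0.95 | 5% | 1.03 | 82% |

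**Simulation check** (2,000 runs per rho, 110 per arm assumed, effect set to give the change score about 80% power). At rho 0.5, 0.7 and 0.9:
- change score: 0.79, 0.81, 0.81
- ANCOVA: 0.89, 0.86, 0.83
- week-4 LVEF alone: 0.79, 0.59, 0.25

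**Unequal SDs.**
- Week-4 SD 1.25 times baseline: variance ratio 0.89 at rho 0.5, 0.98 at 0.7 and 0.95 at 0.9. At rho 0.8 the slope is 0.8 × 1.25 = 1 and there is no gain.
- Week-4 SD 0.8 times baseline: ratio 0.57 at rho 0.5, 0.63 at 0.7 and 0.61 at 0.9, so the gain is larger.

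**Chance imbalance.** If the arms differ at baseline by D, the change-score estimate in that trial is shifted by −(1 − slope)·D. With equal SDs the slope equals rho, so 50%, 30%, 20% and 10% of D remains at rho 0.5, 0.7, 0.8 and 0.9. ANCOVA removes this part. Averaged over randomisations D is zero, so neither method is biased.

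**The case against.** A fair defence is that the planned test is simple, valid and consistent with the two-means sample size formula. Nothing in the article contradicts it. All of that stands. The gain also depends on quantities that the article does not give; it is small at high rho and can vanish if week-4 LVEF is more variable. That stands too, and it limits the size of the point but not its direction.

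Three stronger readings are tempting, and the article supports none of them.
- *Baseline LVEF is discarded.* It is not: it is subtracted. In the simulation the change score far outperforms week-4 LVEF alone at rho 0.7 and 0.9, which could not happen if baseline were unused.
- *The comparison is biased by regression to the mean.* The LVEF ceiling applies to both arms and allocation is random, so regression to the mean is equal in expectation. A chance imbalance shifts the result of one particular trial; it is not a systematic bias.
- *NYHA class is analysed without regard to its order or its baseline.* The chi-square sentence speaks of categorical variables in general and does not name NYHA. It does not say whether week-4 class or change in class is tabulated, and change in class would use baseline. Such detail may sit in an analysis plan that is not shown.

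**Conclusion.** The point holds as one of efficiency. Stage Three fixes an unadjusted *t*-test on change for its primary outcome when a more precise analysis is available from the same data. Under equal SDs and rho between 0.5 and 0.9, both assumptions, the planned test costs the equivalent of 25% down to 5% of the patients. With a week-4 SD 1.25 times the baseline SD the saving is at most about 11% over that range, and nil where the slope equals 1.

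Type I error and unbiasedness under randomisation are not in question. The change is worth making because it is cheap and also deals with chance imbalance, not because the planned result would be wrong. The NYHA part is secondary and presumed.

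**What to change.** In the Stage Three Statistical Analysis paragraph, replace the *t*-test on change with ANCOVA of week-4 LVEF on treatment and baseline LVEF. Report the adjusted difference with its 95% CI. Use the same model for 6MWT and TCM syndrome score, each with its own baseline value.

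State how NYHA class will be analysed. If the chi-square sentence is meant for week-4 class, an ordinal model adjusted for baseline class (II or III) would use both the ordering and the entry class.

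The cost is wording only. Table 5 already schedules these measures at weeks 0 and 4, and the article's trial status gives Stage Three as still to start, so the analysis can be prespecified. If the SDs entered in the sample size formula are those of change in LVEF, the resulting number of patients would remain sufficient under ANCOVA.

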### 3.2. Ethical Issue of Stages Two and Three

The trial is conducted according to the guidelines of the Declaration of Helsinki and is approved by the Ethics Committee of Dongfang Hospital Affiliated to Beijing University of Chinese Medicine (number 201002102). All participants have been asked to provide informed consent before participating in the trial.

### 3.3. Quality Control of Stages Two and Three

Research workbook will be formulated. Before the beginning of this stage, all investigators will be trained and tested according to conformance standard. Drugs in this trial will be identified by pharmaceutical manufacturing sector and prepared in accordance with national technical standards procedures. Drugs will be marked only for clinical trial, which cannot be sold. The investigators in clinical centers will take charge of the usage of drugs. The usage record of drugs should include the following information: quantity, shipment, delivery, acceptance, distribution, recycling, and destruction.

In order to achieve the same detection methods, the physicians for 6MWT evaluation and echocardiography will be trained together. Clinical research associates will test the research progress of all clinical centers.

